Current evidence regarding CBE and CSE stents in AIOD mainly focuses on comparisons with bare metal stents (BMSs). Several studies suggested that patients who received CBE stents had an enduring patency advantage, a lower rate of revascularization, and a similar limb amputation rate compared with those who received BMS [6, 8]. Additionally, another study showed that CBE stents were superior to bare metal balloon-expandable stents for the treatment of common iliac artery (CIA) disease at 3 years regarding primary patency, assisted patency, and secondary patency [10]. However, another study demonstrated that the use of CSE stents has similar early and midterm outcomes compared with BMS in severe iliac lesions, while CSE seemed to have higher midterm patency than BMS only in TASC D subjects [11]. As there is no direct comparison between CSE and CBE stent in AIOD patients, no definitive conclusion can be drawn regarding which type of stent is superior.

The Gore Viabahn endoprosthesis (W. L. Gore and Associates, Flagstaff, Ariz) and LifeStream covered iliac stent (Bard Peripheral Vascular, Inc, Tempe, Ariz) represent one of the most widely used CSE and CBE stents, respectively. This prospective, single-center, parallel, noninferiority, randomized controlled trial aims to compare the safety and efficacy of CSE stents and CBE stents in AIOD patients, with a special focus on midterm and long-term freedom from target lesion revascularization (TLR).

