#### Secondary outcomes

The following secondary endpoints of this study are collected at 1, 6, 12, 24, and 36 months post-index procedure:

(1) Stent and/or surgery related mortality; (2) all-cause mortality; (3) amputation-free survival; (4) acute limb ischemia rate; (5) major adverse cardiovascular and cerebrovascular events (MACCEs); (6) target vessel revascularization (TVR) (TVR is defined as the first revascularization procedure (e.g. PTA, stenting, surgical bypass, etc.) in the target vessel(s)); (7) primary patency (the loss of primary patency is defined as target lesion(s) is determined to be > 50% stenosis or TLR/TLR needed in follow up); (8) primary assisted patency (the loss of primary assisted patency is defined as target lesion(s) is determined to be > 50% stenosis after TLR); (9) secondary patency (the loss of secondary patency is defined as target lesion(s) is determined to be > 50% stenosis after endovascular procedure or surgical bypass TVR); and (10) stent-related complication (e.g., stent kinking or fracture).

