### Statistical analysis

R studio Version 1.2.1335 (http://www.R-project.org) and Empower (www.empowerstats.com, X&Y solutions, Inc., Boston, MA) were utilized for statistical analysis. Categorical data are expressed as numbers and rates, while continuous data are expressed as means ± standard deviation (SD) if they are normally distributed, or median (interquartile range [IQR]) vice versa. Student’s *t* test or Mann-Whitney *U* test is used for univariate analysis of continuous data, and the *χ*^2^ test or Fisher’s exact test is used for categorical data. For primary analyses, multivariate logistic regression is adopted to calculate adjusted odds ratios (ORs) and 95% confidence interval (95% CI) for short-term outcomes. Cox proportional hazard regression analysis is used to generate adjusted hazard ratio (HR) and corresponding 95% CI for long-term outcomes. The primary and secondary end points will be analyzed in the modified intention-to-treat analysis, which includes all subjects undergo randomization and subsequent interventions. Sensitivity analyses of primary and secondary endpoints are performed in the per-protocol population, based on the treatment actually received. The noninferiority margin was set at 10 percentage points for the absolute difference between groups. If the standard of noninferiority was reached, the primary and secondary outcomes were subsequently tested for superiority (*P*<0.05). Noninferiority will be considered proven if conclusions drawn from the intention-to-treat and per protocol analyses are consistent.

Further pre-specified subgroup analyses will be carried out in the following subgroups: TASC II C-D lesions versus A-B lesions, occlusion versus stenosis. Adjustment analyses for primary and secondary endpoints were performed based on the Hochberg method [16]. Multiple imputation was used to handle missing data.

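### The noninferiority-then-superiority step and the Hochberg adjustment take in the harm outcomes as well as the efficacy outcomes, which makes a real harm harder to declare

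*Protocol article*

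**What the plan says.** The Introduction gives the trial a double aim: "randomized controlled trial aims to compare the safety and efficacy of CSE stents and CBE stents in AIOD patients". The Secondary outcomes section has one list of ten items. It opens with "1) Stent and/or surgery related mortality; (2) all-cause mortality; (3) amputation-free survival; (4) acute limb ischemia rate", goes on through MACCE, target vessel revascularization (TVR) and three patency measures, and ends with "10) stent-related complication (e.g., stent kinking or fracture". All ten are collected at five visits from 1 to 36 months.

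Two sentences under Statistical analysis then treat the list as a whole:

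- The step after noninferiority: "If the standard of noninferiority was reached, the primary and secondary outcomes were subsequently tested for superiority", at P<0.05.
- Multiplicity: "Adjustment analyses for primary and secondary endpoints were performed based on the Hochberg method".

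The same section also has provisions with no condition attached. On the analysis set it says "The primary and secondary end points will be analyzed in the modified intention-to-treat analysis". On estimation it says "Cox proportional hazard regression analysis is used to generate adjusted hazard ratio (HR) and corresponding 95% CI for long-term outcomes", with adjusted odds ratios and 95% CIs for short-term outcomes. Chi-square or Fisher tests are named for categorical data.

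**The concern.** Making a test wait for noninferiority, and controlling error across a family of endpoints, both guard against false claims of benefit. For harm the costlier error is the missed signal, and both devices make that error more likely. The two sentences cover the secondary outcomes without distinction, so they cover deaths, acute limb ischemia, MACCE and stent complications.

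Two consequences follow. If noninferiority is not reached, the only sentence on when secondary outcomes are tested for superiority does not come into play, although a reader would then particularly want to know how the stents compare on harm. If noninferiority is reached, a harm outcome is judged after an adjustment that can turn a nominally significant excess into a non-significant one. With about 53 lesions per arm, power for harm is limited before any adjustment.

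**Working it through.** **1. Which outcomes fall under the two rules.** In the order of the Secondary outcomes list:

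| Item | Outcome | Type |
|---|---|---|
| 1, 2 | Related mortality; all-cause mortality | harm |
| 3 | Amputation-free survival | either, as the sponsor classes it |
| 4, 5 | Acute limb ischemia; MACCE | harm |
| 6 to 9 | TVR; primary, primary assisted and secondary patency | efficacy |
| 10 | Stent-related complication | harm |

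The harm/efficacy labels are mine, as the protocol gives none. Both rules name the secondary outcomes or endpoints as a class, and neither lists an exception. Five items (1, 2, 4, 5, 10) are harm outcomes on any reading.

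**2. Number per arm.** The Sample size calculation section gives 53 lesions per group, from 82.2% and 89.1% patency, a margin of 0.10 and 80% power. With unpooled variance and one-sided 0.05:

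n = (0.822×0.178 + 0.891×0.109) × (1.645 + 0.842)² / (0.10 + 0.069)² = 52.7, rounded up to 53.

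This matches the stated figure before any allowance for dropout. After the stated 15% dropout, 53 × 0.85 = 45 remain. I use 53 and show 45 as a check.

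**3. Worst-case effect of Hochberg.** Assumption: the family is the primary endpoint plus the ten secondary endpoints, so m = 11, each counted once. Hochberg compares the smallest P with 0.05/m if no larger P meets its own, looser threshold. With one harm standing alone, that is 0.05/11 = 0.0045. For 0 events in one arm and k in the other, the two-sided Fisher value is P = 2 × C(n,k)/C(2n,k):

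| k (against 0) | P, 53 per arm | P, 45 per arm |
|---|---|---|
| 5 | 0.0566 | 0.0556 |
| 6 | 0.0269 | 0.0262 |
| 8 | 0.0059 | 0.0056 |
| 9 | 0.0027 | 0.0025 |

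Unadjusted, 0 versus 6 is the first split below 0.05. At 0.0045, 0 versus 8 still fails and 0 versus 9 is the first to pass. The thresholds are the same at 45 per arm.

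**4. Power under assumed harm rates.** The protocol gives no harm rates, so these are assumptions. Exact power of the two-sided Fisher test:

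| Assumed rates | 53 per arm: 0.05 / 0.0045 | 45 per arm: 0.05 / 0.0045 |
|---|---|---|
| 5% vs 15% | 27% / 7% | 23% / 4% |
| 5% vs 20% | 55% / 23% | 48% / 16% |
| 5% vs 25% | 78% / 46% | 71% / 35% |

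**5. How often the superiority step would not open.** The primary outcome is target lesion revascularization (TLR) at 12 months, and the protocol gives no TLR rate. Assume freedom from TLR of 95% in both arms. Then SE = √(2 × 0.95 × 0.05/53) = 0.0423, and noninferiority is missed with probability 1 − Φ(0.10/0.0423 − z). That is 24% at one-sided 0.05 and 34% at one-sided 0.025. At 45 per arm (SE 0.0459) it is 30% and 41%. These figures show only that a closed step is not a remote case. They are not predictions.

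**The case against.** A reader might infer that harm is tested only if noninferiority is reached, and otherwise goes untested. The text does not support that. It says what follows when noninferiority is reached, and it does not exclude other comparisons. The modified intention-to-treat analysis of secondary endpoints, the odds and hazard ratios with 95% CIs, and the chi-square or Fisher tests carry no condition. So between-arm estimates of harm are planned in any case. This stands in full and limits the point to the formal superiority test and the adjusted P value.

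A reader might also measure the noninferiority hurdle with the patency rates in the Sample size calculation section. Those are 9-month patency rates, and the primary outcome is 12-month TLR. Reintervention needs worse symptoms as well as restenosis above 50%, so TLR is likely to be rarer than loss of patency. Patency-based percentages do not measure this hurdle, and none is relied on here.

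The Hochberg sentence comes directly after the subgroup sentence and defines no family, so 11 endpoints is one reading. Hochberg is less strict when several P values are small, and mortality, MACCE and amputation-free survival overlap. Both are fair, and the 6-to-9 shift is a worst case. Counting the five visits separately would, on the other hand, enlarge the family.

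Most of the low power comes from 53 per arm: 5% versus 15% has only 27% power even unadjusted. That is true, but it is no reason to reduce the power further.

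Reporting of serious adverse events, annual monitoring and interim analyses lie outside both rules. They protect participants during the trial. They do not define the final comparison of harm, and the stopping sentence names no endpoint.

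Finally, the protocol nowhere says that a non-significant P value will be read as similar safety. That is a risk of the wording and not a stated intention.

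**Conclusion.** The point holds in limited form. The protocol applies one efficacy-claim rule to every secondary outcome, and at least five of the ten are harm outcomes with no exemption. The fault lies in a rule that the document states, not in detail left to an analysis plan. Estimates and unconditional tests remain, so safety is compared. But the formal test for a difference in harm is tied to an efficacy result, and adjustment makes a real harm harder to declare.

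The size depends on a family that the text does not define. In the worst case of 11 endpoints with one isolated harm, the first significant split moves from 0 versus 6 to 0 versus 9 events of 53, and power for an assumed 5% versus 20% falls from 55% to 23%. With a smaller family, or several small P values, the loss is less. This is a matter of analysis wording, not of clinical management, and it should be changed because it can alter what the trial concludes about harm.

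**What to change.** In the Statistical analysis section:

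1. Limit the noninferiority-then-superiority step and the Hochberg family to the efficacy endpoints: TLR, TVR and the patency endpoints, plus amputation-free survival if the sponsor classes it as efficacy.
2. State that the harm outcomes (related and all-cause mortality, acute limb ischemia, MACCE, stent-related complications) are compared between arms whatever the noninferiority result, as event counts and risk differences or hazard ratios with unadjusted 95% CIs.
3. State that no claim of similar safety will rest on a non-significant adjusted P value.

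The cost is two or three sentences, with no new data and no change to conduct. The downside is small: false-positive safety signals would not be controlled for multiplicity, and the report should say so.

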### Monitoring

The monitoring committee consists of biostatisticians, surgeons, investigators, and nurses who are not involved in the conduct of this study or have financial and professional interests. Annual monitoring will be conducted by the monitoring committee. The monitoring committee will provide feedback to investigators and vascular surgeons as soon as there are any problems. Ethics committee and monitoring committee will have access to check the collected data and question the rationality of the study protocol before, during, and after the trial. Classical interim analyses will be performed by an independent statistician who will be a person other than the regular study statistician. The trial will be terminated when one treatment group is significantly superior or inferior to the other treatment group. The final decisions regarding study modifications or stop rest with both ethics committee and monitoring committee. All serious adverse events (SAEs) must be reported as soon as possible. The SAE form contains the following information: identification of the subject, attending surgeon, and description of the SAE (event, beginning and duration, severity, outcome, treatment, or interventions taken). To maintain the quality and safety of trial, unblinding occurs only in exceptional circumstances when knowledge of the actual treatment is essential for further management of the subject.

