### Sample size calculation

We calculated the sample size for this study based on the results of previous studies [4, 13]. As is reported previously in AIOD patients, the 9-month primary patency of CBE stent (BARD®LIFESTREAM™ Stent) was 89.1%, while the 9-month primary patency of the CSE stent (GORE® VIABAHN™ stent) was estimated to be 82.2% based on VIASTAR Trial [14, 15]. In the present study, we hypothesized that the primary patency of CBE stent is not inferior to that of CSE stent; the predetermined noninferiority margin on risk difference scale (δ) is set as 10% between treatment groups. The type I error rate is 0.05, the power of the test is set as 80%, and the randomization ratio is set as 1:1. After accounting for a 15% dropout rate. It was calculated that 53 lesions per group are needed for a total of 106 lesions.

In order to achieve adequate participant enrollment, we will recruit patients by putting up posters or advertising on the Internet, furthermore, we actively recruit patients from outpatient department and emergency department.

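### The interim stopping rule has no boundary while the final superiority test stays at P<0.05; unadjusted looks at that level would raise the superiority/inferiority error to about 8% with one interim and about 13% with three

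*Protocol article*

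**What the plan says.** The Monitoring section of the protocol article announces interim analyses, in the plural and described only as classical, to be run by a statistician independent of the study. The trigger follows: "The trial will be terminated when one treatment group is significantly superior or inferior to the other treatment group". The next sentence leaves the final decision on stopping to the ethics and monitoring committees. On frequency, the section says only "Annual monitoring will be conducted by the monitoring committee", and it does not say that these visits are the interim analyses.

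In the Statistical analysis section, once noninferiority is met, "the primary and secondary outcomes were subsequently tested for superiority", at P<0.05. The Hochberg adjustment named there is for primary and secondary endpoints; it is not a correction for repeated looks. The Sample size calculation section states "The type I error rate is 0.05", within a noninferiority calculation with a 10-point margin.

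**The concern.** Taken together, the two sections set a stopping trigger of *significantly* different and a final test at the full 0.05. Any chance of a false positive spent at an interim look then comes on top of the 5% used at the end. The article names no boundary that would prevent this, and the word classical does not identify one.

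Two things are at stake. The first is the false-positive rate of a claim that one stent is better or worse than the other. The second is the size of the effect reported after an early stop: with few lesions, only a large observed difference reaches nominal significance, so the estimate from a stopped trial is biased away from zero. The Discussion hopes for level 1 evidence for stent selection, so an exaggerated early result would carry weight.

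**Working it through.** **1. Which test the 0.05 in the sample size section belongs to.** Inputs from that section: patency 0.891 (CBE) and 0.822 (CSE), margin 0.10, power 80%.

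n per group = (z₀.₉₅ + z₀.₈₀)² × [0.822×0.178 + 0.891×0.109] / (0.10 + 0.069)² = 6.183 × 0.2434 / 0.02856 = 52.7, so 53.

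The planned 53 is reproduced only with a one-sided 0.05 noninferiority test, and before any dropout allowance (a separate matter). That 0.05 is therefore the noninferiority level. The level for a test of difference is the P<0.05 in the Statistical analysis section.

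**2. Error of the superiority/inferiority conclusion with unadjusted looks.** Assumption: every look, including the last, rejects when |Z| > 1.96. Under no difference the statistics are jointly normal with corr(Zᵢ, Zⱼ) = √(tᵢ/tⱼ), where t is the information fraction. The overall error is P(|Z| > 1.96 at any look).

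| Looks, equally spaced | Two-sided error | In one given direction (nominal 2.5%) |
|---|---|---|
| Final only | 5.0% | 2.5% |
| 1 interim + final | 8.3% | 4.2% |
| 2 interims + final | 10.7% | 5.4% |
| 3 interims + final | 12.6% | 6.3% |

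A single interim at 25% or 75% information gives 9.1% or 7.3%.

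**3. Binary data at the planned size.** The only event rates in the article are the complements of the patency rates: 17.8% and 10.9%, mean (17.8 + 10.9)/2 = 14.35%. With 14.35% in both arms:

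| Test at each look | 1 interim (26, then 53 per arm) | 2 interims | 3 interims |
|---|---|---|---|
| χ², uncorrected | 8.7% | 10.6% | about 12% |
| Fisher's exact | 3.8% | 4.7% | 5.2% |

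These are rates of patency loss. The primary endpoint is TLR, and patency loss also counts stenosis above 50% without TLR, so TLR should be rarer. At an assumed TLR rate of 8%, one interim plus final gives 7.7% (χ²) or 1.9% (Fisher).

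**4. Overstatement after an early stop.** With true rates of 17.8% and 10.9% (6.9 points), a look at 26 per arm reaches P<0.05 in about 12% of trials by χ² (5.1% by Fisher). Among the χ² crossings the mean observed difference is about 21 points, and 21/6.9 is about three times the truth.

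**5. Noninferiority error.** With a true difference of −10 points, 53 per arm and a one-sided 0.05 test, false noninferiority is 5.5–5.6% with no interim. It is 5.5–5.8% with one to three interims under the stated superiority/inferiority stop. It would reach 8.7–15.0% only if noninferiority itself were tested unadjusted at every look, which the article does not say.

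**6. With a boundary.** For two equally spaced looks, critical values 3.29 then 1.96 (Haybittle-Peto) give 0.050, and 2.797 then 1.977 (O'Brien-Fleming) give 0.050. For three looks, Haybittle-Peto gives 0.051 and O'Brien-Fleming (3.471, 2.454, 2.004) gives 0.050.

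**The case against.** The strongest reply is that nothing in the article says the interim tests use P<0.05. *Significantly* is undefined, classical interim analyses could mean a standard group-sequential design, and boundaries commonly sit in an analysis plan or committee charter that is not shown. This stands as far as the size goes: 8% to 13% is conditional. It does not remove the point, because the article does fix a stopping trigger and an unreduced final level and refers to no boundary anywhere. A Pocock boundary, for instance, would also require the final P<0.05 to change.

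A reader might infer that the trial's stated type I error of 0.05 becomes 8–13%. The article does not support that. That 0.05 belongs to the noninferiority test, which the stated stop hardly affects.

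A reader might also take the rule as binding. The following sentence of the Monitoring section gives the decision to the committees, although *significantly* is the only statistical trigger they are given.

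The number of looks is also open. If the annual visits were the interims, the Trial status dates (enrolment June 2020 to June 2022) with even accrual imply no 12-month outcomes at year 1, about half at year 2 and all at year 3. That is one informative interim, so about 8%. Recruitment would then be complete, which weakens any claim that stopping would cut the number enrolled. Three interims is an upper illustration, not something the text supports.

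Lastly, the inflation depends on the test. The Statistical analysis section lists both χ² and Fisher's exact test and names logistic regression for primary analyses. With Fisher throughout, the total in the cases above stays at or near 5%, because that test is conservative at these event counts.

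**Conclusion.** The point holds in conditional form. The article sets a significance-based stopping rule without a boundary beside a final superiority test left at P<0.05. If the interim tests use that same two-sided level, the error of a superiority/inferiority conclusion is about 8% with one interim and up to about 13% with three. This rests on the normal approximation and equally spaced looks; Fisher's exact test gives less. An early stop would also overstate the difference, by about threefold in the worked case, which uses patency-loss rates in place of TLR rates. The noninferiority conclusion is not materially threatened. The sentence should be corrected.

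**What to change.** Replace the termination sentence with a bounded rule and carry it into the committee charter. For example: one interim analysis when half the lesions have 12-month TLR data; the committees are advised to consider stopping for superiority or inferiority only at two-sided P<0.001 (Haybittle-Peto) or at an O'Brien-Fleming boundary; no early claim of noninferiority is made. The final superiority level in the Statistical analysis section should then match the boundary: 0.05 under Haybittle-Peto (total about 0.050), or a critical value of 1.977 under two-look O'Brien-Fleming. The test used at the interim should be named too, since the error depends on it.

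The cost is about one sentence in the Monitoring section and a charter entry, with no additional patients. The downside is that early stopping becomes harder.
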